#### Aim 2: Intervention Cohort (n=25)

An additional 25 infants with SCD under 9 months of age will be recruited for the SCCCD intervention following the same inclusion and exclusion criteria as aim 1. Following the 9-month baseline evaluation, consenting families will participate in the 12-month SCCCD program.

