For aim 2, a pediatric occupational therapist with training in the PAT curriculum will conduct 12 monthly home visits with each enrolled family following the 9-month baseline evaluation. Visit scheduling will allow for up to 15 to 18 months of delivery to accommodate missed visits and ensure all families receive equivalent intervention dosage. Visits will be documented using daily notes that capture completed activities, caregiver engagement, visit duration, and any SCD-related topics reviewed.

For aim 3, semistructured interviews will be conducted with up to 35 caregivers of children enrolled in aim 2. Interviews will be conducted by the method of the participant’s choosing (eg, phone, HIPAA-secure video call, or in person) and are expected to last approximately 30 to 45 minutes. Interviews will be audio-recorded and transcribed verbatim. Two research team members will review all transcripts for accuracy prior to analysis. Caregivers will be compensated for their time.

All data will be stored with 2 levels of password protection. Paper consent documents will be maintained in a locked cabinet in a locked office. Data will be accessible only to the research team.

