### Data Analysis

#### Aim 1

Evaluations will be scored according to their respective manuals. Mixed effects regression will be used to analyze developmental outcome data, with time, group, and time-by-group interaction entered as fixed effects. This approach accounts for within-subject and within-group variability across the 3 longitudinal time points. Scores from the Bayley-4 will be compared to the ASQ-3. Covariates will include race, age, sex, caregiver education, socioeconomic status, disease-modifying medication use, and therapeutic intervention received. The number of evaluations completed and any therapeutic or behavioral interventions received (eg, physical therapy, OT, speech-language therapy) will be documented. Children who receive therapy services during the study period will be analyzed separately.

#### Aim 2

Standardized scores will be calculated for each assessment according to the respective manuals. Scores greater than 1 SD below the mean will be classified as a developmental delay. Repeated measures ANOVA will be used to compare group mean scores at 9, 18, and 30 months. Logistic regression will compare the number of children classified with a delay at 30 months to the aim 1 cohort. The number of caregivers approached and enrolled will be documented, and visits scheduled and completed, along with topics from visit notes, will be summarized. Additional analyses will examine possible changes in the home environment and caregiver mental health before and after the intervention. When the outcome is binary, a mixed effects logistic regression will be used, with time, group, and time-by-group interaction entered as fixed effects and variation of subject intercept as a random effect. Time will also be tested as a random effect in a more elaborate model.

#### Aim 3

Two research team members will use an iterative inductive and deductive thematic analysis approach to review all transcripts and generate themes for a preliminary codebook [60]. The preliminary codes will be applied to 4 interviews using NVivo software; any deviations will be discussed, and the revised codebook will be applied to all remaining interviews [62]. Codes will be analyzed for themes, and participation data from aim 2 will be summarized and integrated with qualitative findings [63,64].

The study protocol and deidentified data will be made available from the corresponding author on request and consistent with the NIH Data Management and Sharing Plan.

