### Missing Data and Attrition

Participants who do not complete all evaluation time points will be analyzed using available data. Attrition will be documented across all aims, including the number of participants who withdraw, are lost to follow-up, or miss individual evaluation visits, and patterns of missingness will be reported.

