## Results

A total of 128 caregivers have been approached, and 72 have consented. Of those, 13 participants withdrew because of time constraints, interest, or loss to follow-up. As of May 31, 2026, a total of 26 unique participants with SCD have participated in aim 1, and 24 unique participants participated in the comparison cohort. For aim 2 with the pilot intervention, 13 caregivers have been approached and 7 have consented, and 5 caregiver or child dyads have been enrolled and have participated. Two caregivers withdrew due to moving out of state or living outside of the intervention radius (>60 miles). Characteristics of participants to date are available in Tables 2 and 3. Enrollment data can be seen in Table 4.

**Table 2. T2:** Caregiver demographics.

Demographics	Sickle cell cohort (aim 1; n=26)	Typically developing cohort (aim 1; n=24)	Sickle cell cohort (aim 2; n=5)
Parental role			
Mother, n	23	22	5
Father, n	3	2	0
Age (y), mean (SD)	30.9 (7.4)	33.4 (5.0)	28.8 (7.9)
Age group (y), n			
20‐29	17	6	2
30‐39	5	15	3
40‐49	4	3	0

**Table 3. T3:** Child demographics.

Demographics	Sickle cell cohort (aim 1), n	Typically developing cohort^a^ (aim 1), n	Sickle cell cohort (aim 2), n
Gender			
Male	13	13	3
Female	13	11	2
Race or ethnicity			
White	0	15	0
Black or African American	25	7	5
Asian	0	1	0
More than one race	1	1	0
Hispanic	0	2	0
Area of Deprivation Index state values			
1‐4 (least deprived)	6	14	1
5‐7	6	5	2
8‐10 (most deprived)	14	4	2

a One participant is excluded in Area Deprivation Index due to being suppressed in the calculation. Values reflect interim enrollment.

**Table 4. T4:** Current study participant enrollment (May 31, 2026).

Enrollment	Sickle cell disease (aim 1)	Typically developing (aim 1)	Sickle cell disease (aim 2)
9 months	12	10	5
18 months	22	15	0
30 months	18	16	0
Total unique participants	26	24	5
Total approach	84	44	13
Total consent	35	37	7

Participants in aim 1 for the SCD cohort all identify as Black or African American; 7 participants in the comparison cohort identify as Black or African American, 15 identify as White, 1 identifies as Asian, and 1 identifies as more than one race.

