### Limitations

Several limitations should be acknowledged. Recruitment is concentrated at a single site, which may limit the generalizability of the findings to SCD programs in other regions. The English-language-only inclusion criterion, necessary given the validation constraints of the assessment measures, excludes non-English-speaking families and limits the diversity of the sample. Aim 2 does not include a randomized comparison condition; developmental outcomes for children who receive the SCCCD intervention will be compared to the aim 1 observational cohort, which introduces the potential for selection bias. Some outcome measures rely on caregiver report, which may be subject to response bias. Finally, participants who do not complete all evaluation time points will be analyzed using available data, and attrition will be documented and reported.

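### Aim 2's repeated measures ANOVA, in its standard form, leaves out children with a missed visit and so conflicts with the protocol's own available-data rule

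*Protocol article*

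**What the plan says.** All references are to the protocol article.

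- **Aim 2 scores** (Data Analysis, Aim 2): "Repeated measures ANOVA will be used to compare group mean scores at 9, 18, and 30 months". The sentence does not say which groups are compared or which term is tested.
- **Missing visits** (Missing Data and Attrition): "Participants who do not complete all evaluation time points will be analyzed using available data". The Limitations section repeats this rule.
- **Aim 1, same measure and same visits** (Data Analysis, Aim 1): "Mixed effects regression will be used to analyze developmental outcome data, with time, group, and time-by-group interaction entered as fixed effects".
- **Aim 2 binary outcomes** (Data Analysis, Aim 2): "When the outcome is binary, a mixed effects logistic regression will be used, with time, group, and time-by-group interaction entered as fixed effects", with a random subject intercept.
- **Timing** (Participants, Aim 2): "Following the 9-month baseline evaluation, consenting families will participate in the 12-month SCCCD program". The Procedures add: "Visit scheduling will allow for up to 15 to 18 months of delivery to accommodate missed visits".
- **Comparator** (Limitations): "developmental outcomes for children who receive the SCCCD intervention will be compared to the aim 1 observational cohort".
- **Evaluations so far**: Table 4 in the Results gives counts by visit as of May 31, 2026.

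**The concern.** A conventional repeated measures ANOVA needs a full row of scores for each child, so a child with two of three evaluations contributes nothing. The available-data rule promises the opposite. An analyst given both instructions has to break one of them, and which one is broken changes who is in the analysis.

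The exclusion would fall mainly on the Aim 1 children, against whom the intervention children are to be judged. Many of them have no 9-month score. Complete-case results are safe only if the children with all three visits are like the rest, in effect missing completely at random. A likelihood-based mixed model keeps the partial records and needs only the weaker missing-at-random assumption.

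A second matter arises as soon as the sentence is rewritten. The 9-month visit comes before any home visit, so the term that carries the intervention effect has to be chosen with that in mind.

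**Working it through.** The article gives no attrition, SD or power figure for this analysis, so there is no stated figure to reproduce. The inputs are the Table 4 counts:

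| Evaluation | SCD, Aim 1 | Typically developing, Aim 1 | SCD, Aim 2 |
|---|---|---|---|
| 9 months | 12 | 10 | 5 |
| 18 months | 22 | 15 | 0 |
| 30 months | 18 | 16 | 0 |
| Sum | 52 | 41 | 5 |
| Unique participants | 26 | 24 | 5 |

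The sums exceed the numbers of unique participants in Aim 1 (52 against 26, 41 against 24), so I read the rows as evaluations done and not as ages at entry.

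**1. Who can be complete, SCD Aim 1.** Without a 9-month evaluation: 26 − 12 = 14, and 14/26 = 54%. Assume that each listed participant has at least one evaluation. Each of the 14 has then been seen at 18 or 30 months and is past the 9-month window (±1 month, Procedures). At most 12 of the 26 can ever have all three.

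**2. Evaluations usable, SCD Aim 1.** At most 12 × 3 = 36 of 52. At least 52 − 36 = 16 are dropped, and 16/52 = 31%. This step does not need the assumption in step 1: at least 22 − 12 = 10 of the 18-month and 18 − 12 = 6 of the 30-month evaluations belong to children with no 9-month score.

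**3. The final SCD cohort.** 50 − 26 = 24 are still to be recruited. If all 24 attend every visit, the ceiling is 12 + 24 = 36 of 50. Without the assumption in step 1, at least 10 children are still certain to be incomplete, and the ceiling is 50 − 10 = 40 of 50.

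**4. Typically developing cohort, in case it is also used.** Without a 9-month evaluation: 24 − 10 = 14 (58%). With k completers and at least one evaluation for each other child, 3k + (24 − k) ≤ 41, so k ≤ 8. At most 24 of the 41 evaluations to date are usable today. Some of these children may still complete later visits.

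**5. The Aim 2 side.** Families start the program after the 9-month evaluation, so that score should be present. If 10% or 20% of the later visits are missed independently (an assumption), 25 × 0.9² ≈ 20 or 25 × 0.8² = 16 of 25 children are complete.

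**6. What a group main effect would estimate.** Let b be a constant pre-existing difference between the groups, and let e18 and e30 be the intervention effects at 18 and 30 months. The effect at 9 months is zero. The difference averaged over the visits is

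M = b + (0 + e18 + e30)/3, so M − e30 = b − (2·e30 − e18)/3.

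Twelve monthly visits from 9 months end at about 9 + 12 = 21 months, and the extended schedule runs to 9 + 15 = 24 or 9 + 18 = 27 months. The 18-month evaluation therefore falls during delivery. As assumed scenarios, M = b + (2/3)·e30 if e18 = e30, and M = b + (1/2)·e30 if e18 is half of e30. With b = 0 the effect is understated. In the second scenario, b above e30/2 overstates it, and b below −e30/2 reverses its sign. The 9-to-30-month difference in change equals (b + e30) − b = e30, free of a constant b.

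**The case against.** **No passage says completers only.** That is true. The restriction follows from the usual form of the named method, and the explicit rule says the opposite. Some analysts use the term loosely for a mixed model, which would remove the conflict. That reading is weak here, because the same section names mixed models separately for Aim 1 and for the binary Aim 2 outcomes.

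**The groups are not named.** The sentence could mean change within the Aim 2 group alone. The Table 4 losses would then not apply, although the conflict with the available-data rule would remain. The Limitations section points to a comparison with the Aim 1 cohort but does not say whether the peers are included.

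**Dilution.** A reader might infer that the ANOVA averages in the baseline visit and so understates any effect. The document does not support this. It names no tested term, and comparisons at each visit or a group-by-time test would avoid the averaging. Even under a main-effect test, baseline imbalance could push the error either way. An unnamed term may be settled in the analysis plan and is not a fault in itself.

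**Precision.** A reader might also apply 12/26 = 46% to all 50 comparators (23 children) and, with 15 to 20 complete intervention children, put the standard error 25% to 35% higher than with 50 and 25. Nothing shows that the 24 future recruits will miss the 9-month visit at that rate. With 36 comparators, √(1/36 + 1/20)/√(1/50 + 1/25) = 1.14, and 1.25 with 15 in place of 20. The benchmark of 50 and 25 fully observed children is also one that a mixed model would not reach, because a child without a 9-month score gives only partial information on change. These ratios are assumed scenarios and do not measure the gain from the fix.

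**Conclusion.** The conflict between the Aim 2 method and the available-data rule is real. On the Table 4 counts, a complete-case ANOVA would discard at least 16 of the 52 SCD Aim 1 evaluations to date (31%). It could use at most 36 of the planned 50 SCD comparators, or 40 if some listed children have not yet had any evaluation. These figures assume that the ANOVA takes its standard form, that it compares Aim 2 with the Aim 1 children with SCD, and that Table 4 counts completed evaluations.

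The concern about the baseline visit is conditional: it applies only if the group main effect is the test, and its direction is not known.

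The severity is moderate. The article describes Aim 2 as a feasibility pilot and makes no confirmatory claim for it. Still, the Bayley-4 is the primary outcome measure and the results are meant to inform a randomised trial, so the sentence should be corrected.

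**What to change.** Replace the ANOVA sentence with the model already planned for Aim 1, for example:

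> Aim 2 scores will be analysed with a linear mixed effects model with visit (9, 18, 30 months) as a three-level factor, group, and group-by-visit as fixed effects, and within-child correlation through a random intercept or an unstructured covariance. All observed visits will be used. The Aim 2 effect is the group-by-visit contrast for change from 9 to 30 months; the group main effect will not be used for this purpose.

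The same text should say which Aim 1 children form the comparison group.

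This keeps partial records under missing at random and brings Aim 2 into line with Aim 1, with its own binary analysis and with the missing-data rule. It does not remove the selection bias that the Limitations section acknowledges: the change contrast cancels a constant baseline difference but not different underlying trajectories.

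The cost is a few sentences of analysis wording and no new data. Table 4 shows no 18- or 30-month Aim 2 evaluations as of May 31, 2026, so on those counts the change would come before any post-baseline Aim 2 score.

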## Methods

### Study Design and Setting

This study is funded by the National Heart, Lung, and Blood Institute under a K23 award designated Independent Clinical Trials Not Allowed (K23HL161328), reflecting the determination by the National Institutes of Health that the proposed research does not constitute an independent clinical trial. Aim 1 is an observational cohort study, and aim 2 is a feasibility pilot intended to inform a future randomized controlled trial. Accordingly, this study was not registered on ClinicalTrials.gov. This study includes 3 aims with different designs, and we selected a reporting guideline for each. We follow the STROBE (Strengthening the Reporting of Observational Studies in Epidemiology) guideline for the aim 1 cohort [28], the TIDieR (Template for Intervention Description and Replication) for the aim 2 SCCCD intervention [29], and the COREQ (Consolidated Criteria for Reporting Qualitative Research) for the aim 3 interviews [30]. We report the protocol following the SPIRIT (Standard Protocol Items: Recommendations for Interventional Trials) 2025 statement [31]. Completed TIDieR and SPIRIT 2025 checklists are provided as Checklists 1 and 2, respectively.

Participants are recruited through Washington University School of Medicine and the Sickle Cell Clinic at St. Louis Children’s Hospital (SLCH), a regional hub for pediatric SCD care that follows over 400 children and receives approximately 25 newborns with SCD annually. For aim 1, we will recruit 100 children, 50 with SCD and 50 demographically matched peers, who will complete developmental evaluations at 9, 18, and 30 months with concurrent caregiver surveys. For aim 2, an additional 25 children with SCD will be recruited to participate in a 12-month home-visiting intervention. Caregivers of children enrolled in aim 2 may also be invited to participate in a qualitative interview as part of aim 3.

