### Participants

#### Aim 1: Incidence Cohort (n=100)

Children with SCD (n=50) under 9 months of age with all SCD genotypes and their caregivers will be recruited from the Sickle Cell Clinic at SLCH. Children without SCD (n=50) will be recruited as a comparison cohort and matched at the group level to the SCD cohort on the distributions of age, sex, race, socioeconomic status, and Area Deprivation Index [32], rather than paired individually. Group-level matching will be finalized after enrollment. Typically developing children will be recruited through SLCH general medicine, community early childhood centers, local pediatricians, public libraries, local early intervention providers, and faith-based organizations, using methods previously successful in this lab [33,34]. Children will be excluded if they have a diagnosis associated with developmental delay that is not attributable to SCD, or if the family is not English-speaking.

Caregivers of children with SCD will be approached by phone or following a regularly scheduled clinic visit. Interested caregivers will review the informed consent document with a member of the research team by phone, Health Insurance Portability and Accountability Act (HIPAA)–secure video call, or in person.

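### The aim 2 delay regression names the whole aim 1 cohort as comparator, half of it without SCD; followed as written, it biases the odds ratio against SCCCD

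*Protocol article*

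**What the plan says.** The Aim 2 paragraph of Data Analysis states: "Logistic regression will compare the number of children classified with a delay at 30 months to the aim 1 cohort". Limitations repeats the comparator and attaches one caveat to it: outcomes "will be compared to the aim 1 observational cohort, which introduces the potential for selection bias".

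Study Design and Setting gives the make-up of that cohort: "we will recruit 100 children, 50 with SCD and 50 demographically matched peers". The Participants section puts both halves under one aim 1 heading with n=100, and adds: "Children without SCD (n=50) will be recruited as a comparison cohort". The aim 2 sample is a further 25 infants, all with SCD.

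Nowhere does the article limit the aim 2 comparator to children with SCD, or say that SCD status enters this regression. In the recruitment text and tables it does separate the two halves by name.

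**The concern.** Aim 2 is meant to evaluate the effect of SCCCD on development in children with SCD and to inform a later randomized trial. Only untreated children with SCD can stand in for what would have happened to the treated children without the program. If half the comparator lacks the disease, the comparator's delay rate is pulled down by the very difference that aim 1 sets out to measure. The treated group then has to make up part of the disease gap before any benefit shows. An ineffective program would look harmful, and a useful one would look weaker than it is, null or harmful. Limitations mentions selection bias, which is a different problem and does not cover this one.

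**Working it through.** The article gives no expected odds ratio, effect size or power for aim 2, so there is no figure of its own to reproduce.

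**Inputs**
- Aim 1 mix: 50 with SCD, 50 without (Study Design and Setting). Table 4 shows a similar mix at 30 months so far: 18 with SCD and 16 without, so 16/34 = 47% without.
- Delay rate in untreated SCD, p_S: 30% to 50% (guideline range cited in the Introduction). The team's earlier work found 50% in children over 12 months.
- Delay rate without SCD, p_N: not given. Assumed 10% to 25%, with 15% as a worked value. Delay is defined as more than 1 SD below the mean, which for a single normally distributed score is about 16%.

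**Formulas**
- Pooled comparator rate: p_C = 0.5 p_S + 0.5 p_N
- OR = [p_T/(1 − p_T)] / [p_C/(1 − p_C)], where p_T is the rate in treated children
- The OR reaches 1 only when p_T = p_C, that is, after a relative reduction of 1 − p_C/p_S

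**Intervention with no effect (p_T = p_S; the correct OR is 1)**

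| p_S | p_N (assumed) | p_C | OR shown | Relative reduction needed to reach OR 1 |
|---|---|---|---|---|
| 30% | 10% | 20.0% | 1.71 | 33% |
| 30% | 25% | 27.5% | 1.13 | 8% |
| 50% | 10% | 30.0% | 2.33 | 40% |
| 50% | 25% | 37.5% | 1.67 | 25% |

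**True 30% relative reduction, p_N = 15%**
- p_S = 50%, p_T = 35%, p_C = 32.5%. Against SCD only: (0.35/0.65)/(0.50/0.50) = 0.54. Against the pooled cohort: (0.35/0.65)/(0.325/0.675) = 1.12.
- p_S = 30%, p_T = 21%, p_C = 22.5%. Against SCD only: (0.21/0.79)/(0.30/0.70) = 0.62. Against the pooled cohort: (0.21/0.79)/(0.225/0.775) = 0.92.

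**When the sign flips.** For a 30% relative reduction the pooled OR exceeds 1 when 0.7 p_S > 0.5 p_S + 0.5 p_N, that is, when p_N < 0.4 p_S. That is below 20% if p_S is 50%, and below 12% if p_S is 30%. Above those values the benefit is diluted but keeps its direction.

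**Baseline scores available.** Table 4 lists 12 aim 1 children with SCD evaluated at 9 months and 18 at 30 months. Even if all 12 are among the 18, at least 18 − 12 = 6 of the children seen at 30 months have no 9-month evaluation.

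**The case against.** The best defence is that the wording is loose and that no pooling is planned. The article also calls each half a cohort, and the binary mixed model for aim 2 has a group term with undefined levels. A three-level factor (treated SCD, untreated SCD, no SCD) would pool nothing, and an analysis plan not shown might specify it. So a reader should not infer that the authors have decided to pool. But the article does not state the three-level reading for this regression, and it names the comparator twice without restriction. If the SCD half is meant, both sentences still need correcting.

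It is also fair to say that the sign reversal is not general. It depends on assumed rates, as the OR of 0.92 shows. If delay means a low score in any one of the five Bayley-4 domains, the non-SCD rate would be above 16% and the bias smaller. The direction of the bias stands as long as the non-SCD rate is below the SCD rate.

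Two further inferences are tempting and not supported:
- **That the repeated measures ANOVA has the same fault.** Its groups are not defined, and it may describe change within the aim 2 children only.
- **That the SCD half comes from a wider catchment than the treated children.** The article says aim 2 recruits "following the same inclusion and exclusion criteria as aim 1", yet Results gives as a reason for withdrawal "living outside of the intervention radius (>60 miles". The two withdrawals are reported for moving or distance combined, and no aim 1 catchment is given. This is a minor inconsistency to reconcile, and the main point does not rest on it.

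Finally, aim 2 is a feasibility pilot of 25 children and its non-randomized comparison is disclosed. That limits how much weight the estimate can bear, but does not make the stated comparator the right one.

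**Conclusion.** The concern holds for the 30-month logistic regression as written. Its stated comparator is half children without SCD, and following it would bias the odds ratio against SCCCD whenever their delay rate is below that of children with SCD. Under the ranges above, an ineffective program would show an OR between 1.13 and 2.33. Whether a beneficial program would appear harmful or only weaker depends on the non-SCD rate, which the article does not give. The documents do not support saying that benefit would always be reversed.

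**What to change.** 1. In Data Analysis (Aim 2) and in Limitations, name the aim 1 children with SCD (n=50) as the comparator for delay at 30 months. Use the same comparator in any aim 2 model that contrasts groups, and state the levels of its group term.
2. Report any contrast between treated children and children without SCD separately, labelled as a benchmark and not as the intervention effect.
3. Do not make adjustment for the 9-month Bayley-4 score a complete-case requirement. At least a third (6 of 18) of the current 30-month SCD comparator would be lost. Keep it as a sensitivity analysis, or use a method that handles missing baselines.
4. Reconcile the 60-mile radius with the statement that the aim 2 criteria are those of aim 1.

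Items 1 and 2 are changes of wording and need no new data. Table 4 shows no aim 2 child yet evaluated at 30 months, so the comparator can still be fixed before that outcome exists. Halving the comparator does not cost useful power in a typical case. For a true fall from 50% to 25% at a two-sided 5% level (assumed), power is about 55% with 25 against 50 children with SCD. It is about 11% with 25 against the pooled 100 (non-SCD rate assumed 16%). The correction removes a bias; it does not make a 25-child pilot precise.

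### The one Aim 2 analysis that names Aim 1 as comparator cuts the Bayley-4 score to delay yes/no at 30 months and lists no 9-month score, so the non-randomised contrast is avoidably imprecise and not adjusted for baseline

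*Protocol article*

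**What the plan says.** All statements are from the protocol article.

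- **Between-cohort comparison (Data Analysis, Aim 2).** "Logistic regression will compare the number of children classified with a delay at 30 months to the aim 1 cohort". The outcome is defined just before: "Scores greater than 1 SD below the mean will be classified as a developmental delay". No covariate or 9-month score is listed; the covariate list in that section stands under Aim 1.
- **Mean scores (same paragraph).** "Repeated measures ANOVA will be used to compare group mean scores at 9, 18, and 30 months". The groups are not defined.
- **Longitudinal binary model (same paragraph).** "When the outcome is binary, a mixed effects logistic regression will be used, with time, group, and time-by-group interaction entered as fixed effects". Here too no cohort is named.
- **Limitations.** "Aim 2 does not include a randomized comparison condition"; instead, "developmental outcomes for children who receive the SCCCD intervention will be compared to the aim 1 observational cohort". The possibility of selection bias is conceded there.
- **Sizes (Study Design and Setting).** "For aim 1, we will recruit 100 children, 50 with SCD and 50 demographically matched peers", and "For aim 2, an additional 25 children with SCD will be recruited to participate in a 12-month home-visiting intervention".
- **Data available.** The Procedures and Table 1 schedule the Bayley-4, the primary outcome measure, at 9, 18 and 30 months in both aims. Missing Data and Attrition says that children with incomplete visits are analysed on whatever data they have.

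**The concern.** The contrast between treated children and the Aim 1 cohort is what would carry preliminary evidence on the intervention into the planned randomised trial. As written, the only analysis tied to that contrast has two weaknesses.

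1. It replaces a graded score by a threshold, so a child just below the cut and a child far below it count the same. With 25 treated children, that loss of information matters.
2. It looks at 30 months only. The cohorts are not randomised, so any difference that existed at 9 months, before treatment, passes into the apparent effect.

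Both weaknesses can be avoided with data already on the visit schedule.

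**Working it through.** The article gives no power, effect size or significance level for Aim 2, so there is no figure of the plan's to reproduce.

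**Inputs from the article:** 25 treated children; 50 Aim 1 children with SCD; delay in 30% to 50% of children with SCD (Introduction).

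**Assumptions:** two-sided 5% test; delay is one normal score cut at a threshold, with the same SD in both groups; 50% delay without intervention and 25% (or 30%) with it; 9-to-30-month correlation r of 0.4 to 0.6; no missing scores; comparator limited to children with SCD.

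**Information kept after the cut.** Relative efficiency = φ(z_p)² / [p(1−p)].
- p = 0.50: 0.3989² / 0.25 = 0.64, a loss of 36%.
- p = 0.30: 0.3477² / 0.21 = 0.58, a loss of 42%.

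**Power, 50% versus 25%.** The same change on the score scale is a shift of 0.674 SD.
- *Cut outcome.* Pooled rate = (50×0.50 + 25×0.25)/75 = 0.417. The standard error is 0.121 under no effect and 0.112 under the alternative. (0.25 − 1.96×0.121)/0.112 ≈ 0.12, so power is about 55%. Simulating the logistic likelihood-ratio test gives 57–58%.
- *30-month mean.* SE = √(1/50 + 1/25) = 0.245 SD. 0.674/0.245 − 1.96 = 0.79, so power is about 79%. Simulated t test: 77%.
- *ANCOVA on the 9-month score.* SE = 0.245 × √(1−r²), which is 0.224 at r = 0.4 and 0.196 at r = 0.6. Power is about 85% to 93%; simulated, 84% to 92%.
- *Change from 9 to 30 months.* SE = 0.245 × √(2(1−r)). Simulated power is about 70% at r = 0.4, 77% at 0.5 and 86% at 0.6, so below r = 0.5 it does worse than the unadjusted mean.

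| Assumed delay rates | Cut outcome | 30-month mean | ANCOVA, r 0.4–0.6 |
|---|---|---|---|
| 50% vs 25% | 57–58% | 77% | 84–92% |
| 50% vs 30% | about 41% | about 56% | 63–75% |

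**Effect of no baseline adjustment.** Suppose no true effect, a 0.5 SD advantage at 9 months in Aim 2 families and r = 0.5 (all assumed). The unadjusted logistic test then rejects about 14–15% of the time instead of 5%.

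**What the ANOVA would retain.** Table 4 shows 9-month evaluations for 12 of the 26 Aim 1 children with SCD, and 18-month evaluations for 22. An analysis that needs all three visits can use at most 12 of those 26. At least 22 − 12 = 10 children have an 18-month evaluation without a 9-month one, and they are past the 9-month window. This fits poorly with the stated intention to use available data.

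**The case against.** The strongest reply is that the same paragraph already plans more. The ANOVA compares mean scores at all three ages, and the mixed logistic model has a time-by-group term. Aim 2 has a single cohort, so a group term needs a second one, and the Limitations section points to Aim 1. A reader might infer from the logistic regression sentence that no continuous or longitudinal comparison with Aim 1 is planned. The article does not support that: both models may well be meant as such comparisons, and nothing makes the 30-month regression primary or sole. They do not remove the concern, however. The group is undefined, the classical ANOVA drops incomplete children, and the mixed logistic model still uses the cut outcome.

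Other objections stand in part:

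- *No covariates listed does not mean none will be used.* True. The article does not exclude adjustment; it only leaves the 9-month score out of the one comparison it ties to Aim 1.
- *Aim 2 is a feasibility pilot.* True, so a reader should not conclude that low power makes the plan wrong. But the article also sets out to evaluate the intervention's effect and to establish preliminary evidence, and that calls for the most precise estimate the data allow.
- *Delay status is clinically meaningful.* True, and a reason to keep reporting it.
- *The size rests on assumptions.* True. The Bayley-4 has five domains, and the article does not say whether the 50% refers to one domain or any. If any, the efficiencies of 0.58–0.64 do not apply as they stand.

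**Conclusion.** The concern holds in a limited form. The comparison that the article explicitly ties to Aim 1 discards about 36–42% of the information in a single roughly normal score and makes no stated use of the 9-month measurement. Under the assumed 50% versus 25% delay rates, moving to the 30-month mean raises power from about 57–58% to 77%, and adding the 9-month score raises it to 84–92%.

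The last step assumes r of 0.4–0.6 and complete baselines. With 12 of 26 Aim 1 children with SCD having a 9-month evaluation so far, the real gain will be smaller. The direction of the loss does not depend on the assumed rates or correlations; its size does. The figures for 25 versus 50 also require that the comparator be the SCD half of Aim 1, which the regression sentence does not say.

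This is an inefficient and loosely specified analysis that should be improved, not an invalid one.

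**What to change.** - Make the main Aim 2 versus Aim 1 contrast the difference in 30-month Bayley-4 scaled score, against Aim 1 children with SCD only, reported with a confidence interval.
- Estimate it from a linear mixed model on all available visits that adjusts for the 9-month score without dropping children who lack it. One way is to keep the 9-month score as an outcome and constrain the group means to be equal at 9 months. ANCOVA on the 9-month score is the equivalent when baselines are complete.
- Do not simply carry over the Aim 1 model with free time, group and time-by-group terms. With complete data and time as categories, its 30-month group difference equals the raw difference in means and is not adjusted for baseline.
- Use this model in place of the repeated measures ANOVA, define the groups in every Aim 2 model, and keep the 30-month delay proportion as supportive.
- State the equal-baseline or linear-adjustment assumption, which is not guaranteed in non-randomised groups. Selection bias on other characteristics remains.

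The cost is analysis wording and programming, with no new visits or data. Table 4 shows five Aim 2 children at 9 months and none yet at 18 or 30 months, so the change can be fixed before any Aim 2 outcome at those ages exists.
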